#### Pain extent and distribution

Participants will mark their habitual pain areas on a standardized anatomical body chart, and the pain pattern is classified using a knee pain map to visually assess changes in pain distribution, providing "spatial dimension" information beyond pain intensity and offering a more comprehensive reflection of pain improvement.

### Psychological outcomes

#### Anxiety and depression

The Hospital Anxiety and Depression Scale (HADS) will be employed to assess emotional status. It comprises two subscales: Anxiety (HADS-A) and Depression (HADS-D), each ranging from 0 to 21 points. Scores ≤ 7 indicate normal status, 8–10 represent borderline abnormal status, and scores ≥ 11 denote abnormal levels [51].

#### Pain catastrophizing

The Pain Catastrophizing Scale (PCS) will serve to measure maladaptive thinking patterns related to pain, and has demonstrated good reliability and validity across diverse cultural and clinical populations [52]. It includes 13 items across three dimensions: rumination, magnification, and helplessness. Each item is rated from 0 (never) to 4 (always), yielding a total score range of 0 to 52. A total score ≥ 30 indicates clinically significant pain catastrophizing tendencies.

### Physical performance

Objective physical function will be assessed using a battery of performance-based tests: the 40-m fast-paced walking test, stair climbing test, and 30-s chair-stand test [53].

#### 40-m fast-paced walk test (40 m-FPWT)

Participants walk 40 m along a flat, unobstructed straight path at their maximum safe speed. The total time is recorded to calculate walking speed (m/s).

#### Stair climb test (SCT)

The time required to safely ascend and descend a flight of nine steps is recorded. Use of handrails or assistive devices is permitted if necessary.

#### 30-s chair-stand test (30CST)

Participants are instructed to perform as many full sit-to-stand cycles as possible within 30 s. Full hip and knee extension is required for each repetition. Assistive devices are permitted if the participant is unable to complete the task independently [54, 55].

### Neuromuscular assessment

#### Muscle strength

As described in the intervention protocol, the 1-RM for leg press and knee extension will be assessed using standard resistance equipment (Nakagym, São Paulo, Brazil). Additionally, the maximum isometric contraction strength of the quadriceps, hamstrings, and gluteus medius will be measured using a handheld dynamometer (Lafayette Manual Muscle Tester, USA). The hamstring-to-quadriceps (H: Q) ratio will be calculated to evaluate muscle strength balance [28].

### Statistical analysis

All statistical analyses will be conducted using SPSS version 27.0 (IBM Corp., Armonk, NY, USA) by statisticians blinded to group allocation. All tests will be two-tailed with a significance level set at *P* < 0.05. Baseline characteristics will be summarized using descriptive statistics. Continuous variables will be presented as mean ± standard deviation (SD) or median (interquartile range), depending on data distribution. Categorical variables will be expressed as frequencies and percentages. All efficacy analyses will follow the intention-to-treat (ITT) principle. The primary analysis will focus on evaluating whether the longitudinal response trajectory of the combined PNE + BFRT group differs from those of the comparison groups over time. To address this objective, linear mixed-effects models (LMMs) will be used for repeated-measures analyses of the primary and secondary outcomes. The primary inference of interest will be based on the group-by-time interaction effect, which reflects differential changes in outcome trajectories between intervention groups throughout the study period. To reduce the risk of type I error inflation, KOOS₄ will be considered the sole confirmatory primary outcome, while all other outcomes will be treated as secondary or exploratory. If a significant group-by-time interaction is identified for KOOS₄, post-hoc pairwise comparisons with Bonferroni correction will be performed. Secondary outcomes will be analyzed using similar mixed-effects modeling approaches. Estimated marginal mean differences with 95% confidence intervals will be reported where appropriate. Missing data will be assumed to be missing at random and handled using maximum likelihood estimation within the mixed-effects modeling framework. A supplementary per-protocol analysis, including participants with at least 80% adherence to the intervention, may also be conducted.

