### Sample size

The sample size was estimated using G*Power software (version 3.1.9.7, Franz Faul, Universität Kiel, Germany). The primary outcome is the KOOS₄ score (mean score of the Pain, Symptoms, Activities of Daily Living, and Knee-Related Quality of Life subscales) from the Knee Osteoarthritis Outcome Score (KOOS). Based on previous research, a 10-point improvement in KOOS₄ was considered the Minimum Clinically Important Difference (MCID), with an anticipated Standard Deviation (SD) of 15 points [41, 42]. The following parameters were utilized for the sample size calculation: Significance Level (α) = 0.05, Statistical Power (1-β) = 0.90, Effect Size (Cohen's f) = 0.34, and Number of Groups = 4. The calculations indicated that the minimum total sample size required to detect this effect was 128 cases. Considering an anticipated attrition rate of approximately 15% and to ensure equal and balanced allocation across four groups, the total sample size was increased to 148 participants, resulting in 37 participants per group. This approach enhances the stability and reliability of the study results, ensuring that the research objectives will be successfully met.

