### Primary outcome

#### KOOS_4_

The primary outcome is the between-group difference in longitudinal change in KOOS₄ across all assessment time points. KOOS_4_ was selected as the primary outcome measure because persistent CPSP after TKA affects not only pain intensity but also broader dimensions of knee-related symptoms, activities of daily living, and quality of life, making patient-centered assessment essential when evaluating treatment outcomes. It is one of the most widely used and validated assessment tools in patients undergoing TKA [28].

The KOOS₄ is calculated as the mean of four KOOS subscales (Pain, Symptoms, Activities of Daily Living, and Knee-Related Quality of Life), excluding the Sport/Recreation subscale. Scores range from 0 to 100, with higher scores indicating better knee-related function [47, 48]. Based on prior literature, A between-group difference of 10 points is considered the MCID and will be used to interpret the clinical relevance of observed effects [42].

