The development and progression of CPSP are influenced by multiple factors, among which psychological factors and chronic inflammatory responses are considered major contributors [58–62]. To avoid anticipated pain, patients often limit or avoid physical activity, a behavior that may ultimately lead to functional decline, muscle atrophy, and heightened pain sensitivity. Decreased muscle strength and the persistent accumulation of abnormal or elevated biomechanical loads may cause joint or tissue damage, further exacerbating pain and ultimately forming a vicious cycle of pain, fear, avoidance, functional loss, and renewed pain [63–66]. PNE, as a psychological intervention designed to reshape patients' perceptions of pain and coping strategies, positively influences pain experiences by explaining the biological and physiological mechanisms involved in pain. It has demonstrated small to moderate efficacy in chronic musculoskeletal pain [23, 67–69]. Among patients with persistent chronic pain one year after TKA, PNE has been shown to have clinical significance for pain relief, but its role in improving function remains relatively limited [28]. BFRT, a low-intensity exercise modality that applies external pressure to the proximal limb to partially restrict arterial blood flow and occlude venous return, has attracted significant interest for its exceptional efficacy in inducing muscle adaptation and analgesia. The pain-relieving mechanism is believed to be associated with metabolic stress–induced endogenous opioid release and inflammatory modulation [38, 70–72]. Although BFRT demonstrates promising clinical prospects in various chronic pain and postoperative rehabilitation, no study has yet systematically evaluated its efficacy in patients with CPSP following TKA. Given the potential complementary mechanisms between PNE and BFRT, it is reasonable to hypothesize that combining PNE with BFRT may produce synergistic effects in pain reduction and functional improvement, potentially offering superior clinical benefits for patients with CPSP following TKA.

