To the best of our knowledge, this is the first study to compare the effects of PNE and BFRT in patients with persistent chronic pain one year after TKA and to assess whether combining both approaches yields superior clinical outcomes. Should the final results demonstrate that the combined group significantly outperforms either single intervention group, it would strongly support the clinical application of this integrated rehabilitation strategy. If effective, the combined intervention may provide an integrated non-pharmacological rehabilitation strategy targeting both psychological and physical contributors to CPSP following TKA. It is noteworthy that patients undergoing TKA typically experience a natural trend toward pain resolution within three months to one year post-surgery [73], which may interfere with the interpretation of short-term intervention efficacy. Therefore, this study specifically recruits individuals who continue to experience CPSP one year postoperatively, aiming to minimize the influence of natural recovery and improve the accuracy of treatment-effect evaluation.

However, this study still has several limitations. Firstly, the relatively long follow-up period may increase the risk of participant dropout, potentially affecting the representativeness and the statistical power of the final sample. To mitigate this issue, strategies such as regular communication, progress feedback, and incentive-based engagement will be implemented during the study to enhance participant compliance and ensure data completeness. Secondly, this study primarily focuses on validating clinical efficacy and does not delve into the potential molecular mechanisms underlying the synergistic effects of PNE and BFRT. This direction warrants further exploration in future research. Finally, the four groups differ in therapist contact and supervision, and no attention-matched comparator is included. Consequently, non-specific effects related to therapist attention, supervision, treatment expectations, and therapeutic interaction cannot be completely separated from the specific effects of the interventions. Although intervention exposure and protocol deviations will be documented, the findings should be interpreted as the effects of the respective intervention strategies as delivered. Future studies incorporating attention-matched comparators are warranted to better isolate specific intervention effects.

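### The confirmatory KOOS4 test is a four-arm omnibus interaction that does not single out the combined arm, and it gates the comparisons that do

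*Protocol article*

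**What the plan says.** The Statistical analysis section gives the aim of the primary analysis as a comparison of the combined arm's course with those of the other groups. It then fixes the test: "The primary inference of interest will be based on the group-by-time interaction effect". The Abstract names the same effect as the primary outcome, and the KOOS4 paragraph defines that outcome as a between-group difference in change "across all assessment time points". KOOS4 is the only confirmatory outcome. If the interaction is significant, "post-hoc pairwise comparisons with Bonferroni correction will be performed"; the article does not list the pairs.

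The Introduction hypothesises that the combination is better than either intervention alone and than usual care. The Discussion ties support for clinical use to a finding that the "combined group significantly outperforms either single intervention group". The Sample size section uses "Significance Level (α) = 0.05, Statistical Power (1-β) = 0.90, Effect Size (Cohen's f) = 0.34, and Number of Groups = 4".

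**The concern.** The question concerns one arm against named comparators. The test that decides it concerns any difference in trajectory among any of the four arms. A significant interaction can arise because BFRT works and PNE adds nothing to it, or because every active arm beats usual care by the same amount. Either would be a positive result on the sole confirmatory test, without any evidence for the combination over a single component.

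The comparisons that would supply that evidence have post-hoc status, wait on the omnibus result, and pay a multiplicity correction that the trial's claim does not need. A claim that the combination beats both single arms already requires both tests to succeed.

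**Working it through.** **Inputs from the protocol article.** SD 15, target difference 10 points and 128 evaluable, so 32 per arm (Sample size); baseline plus weeks 12, 24, 36 and 48 (Outcomes); two-sided 0.05 (Statistical analysis).

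**Assumptions not in the article.** Visit is categorical, so the interaction has (4−1)×(5−1) = 12 df. Correlation is compound-symmetric with ρ = 0.5 (range 0.3 to 0.7). Effects are sustained from week 12 to week 48, no data are missing, and Bonferroni covers all six pairs.

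**1. The plan's own figure.** One-way four-group ANOVA: λ = f²N = 0.34² × 128 = 14.80 on 3 and 124 df gives power 0.904. The stated 128 is reproduced, as the size for an omnibus test. With SD 15 and a widest gap of 10 points, the largest possible f is 5/15 = 0.333, with two arms at 0 and two at 10, so the combined arm ties with another arm. If the combined arm alone is 10 higher, f = 10 × √(3/16) / 15 = 0.289 and power at 128 is 78%. The article does not say which pattern of means lies behind 0.34.

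**2. When is the interaction positive?** λ = n × A × T / [σ²(1−ρ)].
- T = 10² × 0.8 = 80, where 0.8 is the sum of squared deviations of (0,1,1,1,1) from its mean.
- A is the same sum for the arms: 1.00 for two against two, 0.75 for one against three.
- The 5% critical value of chi-square on 12 df is 21.03.

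| True pattern | λ at ρ = 0.5 | Interaction significant (ρ 0.3 to 0.7) |
|---|---|---|
| BFRT = combined = +10, others 0 | 32×1.00×80/112.5 = 22.76 | 91% (77 to 99.5%) |
| All three active arms +10 | 32×0.75×80/112.5 = 17.07 | about 80% (61 to 97%) |
| Only combined +10 | 17.07 | about 80% (61 to 97%) |

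The chi-square formula gives 79% for the last two rows; simulation gives 78 to 80%. These rows have the same λ, so the test responds identically whether only the combination works or all three active arms work equally.

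**3. Is a false claim let through?** With BFRT equal to the combination, a six-pair Bonferroni test wrongly favours the combination over BFRT with probability at most 0.05/6/2 = 0.4%. Simulation through the gate agrees (about 0.4%).

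**4. Power when only the combined arm gains 10.** Success means beating both single arms. Each row uses the same summary under both rules, ρ = 0.5. Standard errors of a two-arm difference are:
- raw week 12: 15√(2/32) = 3.75
- baseline-adjusted week 12: 15√(1−ρ²)√(2/32) = 3.25
- baseline-adjusted follow-up average: 15√[(1+3ρ)/4 − ρ²]√(2/32) = 2.30

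| Summary | Gate + six-pair Bonferroni | Both at 0.05, no gate |
|---|---|---|
| Raw week 12 | 27% | 63% |
| Adjusted week 12 | 45% | 78% |
| Adjusted average | 76% | 98% |

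For the adjusted average the figures are 59% against 98% at ρ = 0.3, and 95% against 99.8% at ρ = 0.7. With a three-pair correction the gated figures at ρ = 0.5 are 37%, 54% and 77%. In the last row nearly all the loss is the gate: the gated path cannot exceed the interaction's own power of about 80%.

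**The case against.** Four points can be made for the plan.

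First, a reader might infer that the plan licenses a false superiority claim. It does not. The pairwise step is Bonferroni-corrected and the Discussion rests its clinical conclusion on that comparison, not on the interaction. The false-claim rate of about 0.4% confirms this. This point stands in full and limits the finding.

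Second, a reader might set 27% beside 98% and conclude that the gate and correction waste most of the power. That comparison also changes the visit summary and the baseline adjustment. On a common summary the loss exceeds half only for raw week-12 scores, and at ρ = 0.7 the adjusted average loses little.

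Third, the family of pairs, the visit tested and the coding of time are matters that an article may leave to the statistical analysis plan. That stands: their absence is no finding, and six pairs, week 12 and 12 df are assumptions here. What the article does fix is the omnibus test as primary and the gate in front of the pairs, and those do not match its own stated aim.

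Fourth, a reader might object that synergy is never tested. The hypothesis is superiority over each comparator. That "combining PNE with BFRT may produce synergistic effects in pain reduction and functional improvement" is put forward in the Discussion as a possibility, not as the primary objective, so the missing synergy contrast is not a defect of the primary analysis.

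**Conclusion.** The concern holds as a mismatch between the stated question and the confirmatory test, together with an avoidable loss of power. On the assumptions listed, the primary test would be positive in roughly 80 to 91% of trials at ρ = 0.5 in which the combination adds nothing to BFRT. A truly superior combination would lose 22 percentage points of power on the adjusted average (98 − 76), 33 on adjusted week 12 (78 − 45) and 36 on raw week 12 (63 − 27). The first of these losses runs from 39 points at ρ = 0.3 to about 5 at ρ = 0.7. The mismatch does not depend on the correlation; the sizes do. Because the corrected pairs protect the pairwise claim, this should be fixed but does not invalidate the trial.

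**What to change.** In the Abstract, the KOOS4 primary outcome paragraph and the Statistical analysis section, replace the interaction as primary inference with prespecified contrasts from the same mixed model:
- combined minus PNE, and combined minus BFRT
- combined minus control as well, if the claim over usual care in the Introduction is kept.

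Use one summary fixed in advance. The baseline-adjusted KOOS4 difference averaged over weeks 12, 24, 36 and 48 keeps the intention of covering every visit; week 12 is an alternative. Claim superiority only if every named contrast is significant at two-sided 0.05. This intersection-union rule needs neither Bonferroni nor an omnibus gate. Report the group-by-time interaction and the visit-wise differences as secondary. If synergy is to be discussed, report combined − PNE − BFRT + control with its confidence interval as a secondary estimate.

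The cost is wording and a registry update before any unblinding. There are three trade-offs:
- An average answers a slightly different question from a trajectory test and is less sensitive to an effect that fades.
- When BFRT equals the combination, the chance of a false claim in the combination's favour rises from about 0.4% to at most 0.05/2 = 2.5%, the usual level for a two-sided 0.05 test.
- A smaller advantage is not rescued. With true gains of 0, 5, 5 and 10 points for control, PNE, BFRT and combined, and ρ = 0.5, testing both contrasts directly on averaged change succeeds in 23% of trials, against 6% through the gate.

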Research indicates that therapeutic exercise can attenuate pain sensitivity in both motor and non-motor areas [31–33]. As exercise intensity and duration increase, the effect of inducing pain reduction becomes increasingly pronounced [34–36]. However, for patients with CPSP following TKA, engaging in prolonged high-intensity exercise may pose significant challenges. Blood Flow Restriction Training (BFRT) is a low-intensity training method that partially restricts arterial blood flow and blocks venous return by applying external pressure to the proximal end of the limb [37]. Emerging evidence suggests that BFRT can produce muscle hypertrophy, strength gains, and analgesic effects comparable to those achieved with high-intensity resistance training while imposing substantially lower mechanical stress on the joint [38–40]. Nevertheless, BFRT primarily targets physical and neuromuscular impairments and may not adequately address maladaptive pain-related cognition or fear-avoidant behaviors.

Accordingly, combining PNE with BFRT may offer a complementary rehabilitation strategy. PNE may enhance psychological readiness for rehabilitation by reducing pain-related fear, catastrophizing, and perceived threat associated with movement, whereas BFRT may promote functional recovery and pain relief. To date, no randomized controlled trial has investigated whether combining PNE and BFRT provides superior clinical benefits in patients with established CPSP following TKA. Therefore, this study is designed as a Randomized Controlled Trial to compare the effects of Control, PNE, BFRT, and combined PNE + BFRT on pain, psychological outcomes, physical performance, and knee-related function in patients with CPSP after TKA. We hypothesize that participants receiving the combined PNE + BFRT intervention will demonstrate greater improvements in knee-related function, pain intensity, psychological outcomes, and physical performance compared with those receiving either intervention alone or usual care.

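### Single-step Bonferroni for the pairwise KOOS₄ comparisons is valid but gives up power that Holm's step-down would recover over the same family, with the same error guarantee and no extra patients

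*Protocol article*

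**What the plan says.** The Statistical analysis section makes the KOOS₄ group-by-time interaction the primary inference. If it is significant, "post-hoc pairwise comparisons with Bonferroni correction will be performed". On the level it says "All tests will be two-tailed with a significance level set at" 0.05. It does not state how many pairwise comparisons there are, or whether they concern whole trajectories, one visit or every visit.

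The clinical claim is pairwise. The Introduction hypothesises greater improvement with the combination "compared with those receiving either intervention alone or usual care". The Discussion ties support for clinical use to the case where the "combined group significantly outperforms either single intervention group".

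The Sample size section is built on a four-group global test: "Statistical Power (1-β) = 0.90, Effect Size (Cohen's f) = 0.34, and Number of Groups = 4". It takes 10 KOOS₄ points as the clinically important difference, "with an anticipated Standard Deviation (SD) of 15 points", and concludes that "the minimum total sample size required to detect this effect was 128 cases".

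**The concern.** Bonferroni compares every p value with the same threshold, 0.05 divided by the number of comparisons, however many of the others have already been rejected. Holm relaxes the threshold after each rejection. That costs nothing in the family-wise error guarantee and needs no assumption about how the tests are correlated.

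The difference matters most when several comparisons must succeed together. Beating both single interventions is such a case. The sample size was set for the global test, so power for the pairwise claims is already thin, and a correction that discards part of it should be chosen deliberately.

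**Working it through.** **Inputs.** From the protocol article: two-sided α 0.05, power 0.90, f 0.34, four groups, 10 points, SD 15, minimum total 128, so 128/4 = 32 per arm. Assumptions, because the article does not fix them: normal data, one KOOS₄ contrast per pair with SD 15, and a 3-df global F test at 5% as the gate. The family is either all six pairs or the three combined-arm comparisons.

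**The plan's own figure.** One-way ANOVA with noncentrality N·f² and df 3 and N − 4: at N = 128, 128 × 0.34² = 14.8, and power is 90.4%. The smallest N reaching 90% is 127, or 128 with equal groups. The stated 128 reproduces.

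**Power of one pairwise test.** The standard error of a difference is 15 × √(2/32) = 3.75, so 10 points gives noncentrality 10/3.75 = 2.67. On 124 df:

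| Level | Power |
|---|---|
| 0.05 | 75.4% |
| 0.05/3 = 0.0167 | 59.6% |
| 0.05/6 = 0.0083 | 49.6% |

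**Why Holm cannot do worse.** Order the m p values from smallest to largest. Holm compares the k-th with 0.05/(m − k + 1) and stops at the first failure. The first threshold is Bonferroni's 0.05/m and all later ones are larger. Every Bonferroni rejection is therefore a Holm rejection, whatever m is.

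**Chance that the combined arm beats both single arms** (simulated, gate included; means in the order Control/PNE/BFRT/combined):

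| True means | Six pairs: Bonferroni | Six pairs: Holm | Six pairs: gated Shaffer | Three comparisons: Bonferroni | Three comparisons: Holm |
|---|---|---|---|---|---|
| 0/0/0/10 | 33% | 38% | 44% | 44% | 57% |
| 0/5/5/15 | 33% | 40% | 44% | 44% | 61% |
| 0/0/10/20 | 50% | 62% | 63% | – | – |
| 0/5/5/10 | 3% | 4% | 5.5% | – | – |

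At 0/5/5/10, the chance of showing all three combined-arm differences goes from 5.1% with Bonferroni to 11.4% with Holm over the three-comparison family.

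At 0/0/0/10 with six pairs, power per true difference goes from 49.3% to 52.1% with Holm, and power for all three true differences from 25.0% to 30.3%. With three comparisons, the corresponding gains are 57.7% to 65.3% and 34.8% to 52.0%.

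**How much of the 5% Bonferroni uses.** If four arms are not all equal, the equal ones can form at most one group of three, which gives three true pairwise nulls. With six comparisons on the gated quantity the bound is then 3 × 0.05/6 = 2.5%; with one arm different the simulation gives 2.2%. In other situations the figure changes:

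- All four arms equal: about 3.7% with a 3-df gate. With a 12-df interaction gate it is 3.0% for whole-trajectory pairwise tests and 1.3% for one contrast per pair.
- Three combined-arm comparisons: bound 2 × 0.05/3 = 3.3%, simulated 3.2%.
- Six pairs at one visit, arms differing only at other visits: up to 4.2%.
- All pairs at four follow-up visits, divisor 24: 2.2% if one arm differs at every visit, 3.6% if it differs at one visit only.
- All visits, but divisor 6 within each visit: up to 7.7%.

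**The case against.** Bonferroni is valid, conventional and prespecified, and it contradicts nothing in the document. That stands: choosing Holm is a gain in efficiency, not the repair of a fault.

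A reader might infer that Bonferroni here never spends more than about half of the 5%, or that dividing by six is always twice as strict as needed. The document does not support either. Both need six pairwise comparisons on the same quantity as the interaction gate, with at least one arm truly different. The article states neither the number of comparisons nor their quantity, and under other readings the error ranges from 1.3% to 7.7%. In the 7.7% case, correction within each visit only, the plan would be too liberal, and Holm, which rejects at least as often, would not help. So the family has to be stated together with the method.

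The gain from Holm alone over six pairs is modest, 33% to 38% at 0/0/0/10, and negligible in absolute terms at 0/5/5/10. Narrowing the family does as much: at 0/0/0/10, Bonferroni over three comparisons reaches the same 44% as gated Shaffer over six. Both points stand, and are why the fix pairs Holm with a stated, preferably smaller, family.

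Finally, Bonferroni has matching simultaneous intervals and Holm has no simple ones. The plan reports 95% intervals and reads effects against a 10-point difference, so this is a real, though small, cost.

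**Conclusion.** The point holds as a cheap, worthwhile improvement. Over any fixed family, Holm gives the same family-wise guarantee as Bonferroni, never rejects less and needs no patients.

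With the combined arm 10 points above each single arm, the chance of beating both rises by about 5 to 7 percentage points over six pairs and about 13 to 17 points over three comparisons. With 5-point differences from the single arms, power stays low under either method. These sizes rest on 32 analysed per arm, SD 15, one KOOS₄ contrast and a 3-df gate. That Holm rejects at least as much does not depend on them.

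**What to change.** In the Statistical analysis section, replace 'with Bonferroni correction' by 'with Holm step-down correction'. State one family that covers every comparison and visit used for the confirmatory claim, preferably the combined arm against each of the other three.

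Shaffer's gated step-down (divisors 3, 3, 3, 3, 2, 1 for six pairs) is optional, and only if the pairwise nulls are the same trajectory hypotheses as the interaction gate. For single-visit or time-averaged contrasts, use plain Holm.

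The cost is a sentence, made before unblinding. The step-down is a hand calculation from the unadjusted p values, and the sample size stays at 148. If Bonferroni-width intervals are shown alongside, add a note that they are conservative and may include zero for a comparison that Holm rejects.
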